#### Sample size

We aim to recruit *N* = 681 participants. The sample size calculation is based on an a-priori power analysis, considering the smallest effect of interest as a reference [47]. Our goal is to obtain .95 power, with α = .01 (Bonferroni-corrected p-value for five outcomes; see below), to be able to detect also small effects (or differences) of f = .175 with univariate analyses of variance (one-way). We will only recruit participants who are UK residents and older than 18 years. We introduce the former selection criterion (i.e., being a UK resident) as we will apply definitions of disability and violent crime (see Manipulated variables–experimental stimuli) that are provided by UK institutions.

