#### Confirmatory analyses

We will test for median absolute deviation to detect potential univariate outliers for all outcome variables [49]. We do not plan to exclude outliers but will report their presence. Mean scores and standard variations of as well as bi-variate correlations between all measures will be calculated.

Examining Hypothesis 1a-e (i.e., the effects of person-first language), we will test the assumptions for univariate analysis of variances (ANOVA) for all five outcome measures separately for each of the two descriptor pairings (see Huang [50] who suggests multiple ANOVAs with p-values that are corrected for multiple comparisons rather than a multivariate analysis of variance). Once assumption checks confirmed the suitability of the tests, we will conduct five two-tailed ANOVAs, comparing the indices of positive and negative stereotyping, dehumanization, negative affect, and approach behavior intentions between the identity-first, person-first, and control condition regarding the descriptor pairing “people with a physical disability/the physically disabled”. The analyses will then be repeated for the descriptor pairing “people who have committed a violent crime/violent criminals”. Planned contrasts will be used to investigate for each descriptor pairing whether average negative outgroup perceptions and affect are lower, positive perceptions and approach behavior intentions are higher in the person-first as compared to the identity-first language condition. It is further expected that negative outgroup perceptions and affect are lowest as well as positive perceptions and approach behavior intentions are highest in the control condition. Effect sizes and confidence intervals will be computed. To correct for the multiple ANOVAs in each descriptor pairing, p-values are adjusted using the Bonferroni correction. We address concerns about the reduced power of the tests by using the corrected p-value of p = .01 (i.e., .05 divided by five) in the a-priori power analysis (see above).

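### Holm's step-down procedure would give more power than single-step Bonferroni for the five outcomes at the same family-wise error: a cheap improvement, not an error in the plan

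*Protocol article*

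**What the plan says.** All references are to the protocol article.

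- **Tests.** Under Confirmatory analyses the authors write "we will conduct five two-tailed ANOVAs", one per outcome index. Each compares the outcome "between the identity-first, person-first, and control condition". The set is run for the physical-disability pairing and repeated for the violent-crime pairing.
- **Correction.** "To correct for the multiple ANOVAs in each descriptor pairing, p-values are adjusted using the Bonferroni correction". The family is the five ANOVAs within one pairing.
- **Power cost.** The plan sees the cost and answers it through the sample size: "We address concerns about the reduced power of the tests by using the corrected p-value of p = .01", which it derives as .05 divided by five.
- **Sample size.** The Sample size section follows through: "Our goal is to obtain .95 power, with α = .01 (Bonferroni-corrected p-value for five outcomes; see below", for "small effects (or differences) of f = .175 with univariate analyses of variance (one-way". The resulting target is "We aim to recruit *N* = 681 participants".

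The two sections agree with each other on the corrected level of .01.

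**The concern.** Bonferroni holds every outcome to .01 even after other outcomes in the family have clearly been rejected. Holm relaxes the threshold as rejections accumulate, with the same error guarantee and no further assumption about how the outcomes correlate. The difference is largest when several effects are real, and The present research predicts exactly that: Hypotheses 1a to 1e expect a benefit of person-first language on all five outcomes. Each outcome is its own lettered hypothesis, so power for each one matters, and not only the chance that at least one is significant. At stake are true effects reported as non-significant that an equally strict rule would have detected.

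**Working it through.** **Inputs from the protocol.** Family-wise level .05, five outcomes, three groups per ANOVA, f = .175, target power .95, N = 681, five arms (Manipulated variables), simple randomization (Design plan).

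**Assumptions, not in the protocol.** Equal allocation; between-outcome correlation of .3 or .6; the same f on every outcome that has an effect; no loss to the planned exclusions.

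**Step 1: the plan's own figure.** Power of a one-way ANOVA follows from the noncentral F distribution with noncentrality N × f².
- N = 681, three groups: 681 × .175² = 681 × .030625 = 20.86. Power at α = .01 is .951.
- The smallest N that reaches .95 is 679, or 681 in equal groups of 227. The stated figure is reproduced.

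**Step 2: what each ANOVA will have.** The 681 are the total over five arms, and each ANOVA uses three of them.
- 681 / 5 ≈ 136 per arm; 681 × 3/5 ≈ 409 per ANOVA.
- 409 × .030625 = 12.53. Power at α = .01 is .74.

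**Step 3: the two rules.** Order the p-values p(1) ≤ … ≤ p(5).
- Bonferroni rejects any outcome with p ≤ .05/5 = .01.
- Holm compares p(j) with .05/(6 − j), that is .01, .0125, .0167, .025 and .05 in turn, and stops at the first failure.

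The first Holm threshold equals the Bonferroni threshold, so the chance of at least one rejection is essentially the same under both.

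**Step 4: simulation of the omnibus ANOVAs.** 20,000 repeats per setting, 136 per arm, f = .175 on the true effects. The Monte Carlo standard error is at most √(.25/20,000) = .0035.

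| True effects | Correlation | Power per true effect, Bonferroni → Holm | All true effects rejected, Bonferroni → Holm |
|---|---|---|---|
| 1 | .3 | .741 → .742 | same as per effect |
| 1 | .6 | .736 → .736 | same as per effect |
| 3 | .3 | .734 → .773 | .462 → .549 |
| 3 | .6 | .736 → .770 | .541 → .618 |
| 5 | .3 | .740 → .841 | .335 → .618 |
| 5 | .6 | .736 → .823 | .446 → .684 |

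**Step 5: error control.** With no true effect, both rules have the same family-wise error: .047 at correlation .3 and .040 at .6. With three true effects it is .021 and .019 for Bonferroni, against .041 and .037 for Holm. Holm uses more of the .05 and stays within it.

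**Step 6: the size the plan intended, 227 per group.** With all five effects real and correlations of .3 to .6, per-outcome power goes from .95 to .98, and the chance that all five are significant from .81-.85 to .94-.95. With three real effects, per-outcome power goes from .95 to .96.

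**The case against.** **Bonferroni is valid, prespecified, correctly computed and consistent across sections.** This stands. Nothing here is stated wrongly, and the point is one of efficiency.

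**The plan has already paid for the correction.** It says so: "using the corrected p-value of p = .01 (i.e., .05 divided by five) in the a-priori power analysis". This stands only in part. The .95 holds for a single ANOVA with 681 people, whereas each ANOVA will have about 409 before exclusions. The shortfall to .74 is due to the number of arms, not to Bonferroni, and must not be counted against the correction.

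**Bonferroni offers something in return.** A reader might infer that it gives up power for nothing. The protocol does not support that: it plans confidence intervals, and a fixed .01 threshold pairs directly with 99% simultaneous intervals. Holm has no such simple match. The return is modest, since no interval level is stated, but it is real.

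**Larger gains can be quoted for the contrasts.** For person-first against identity-first, at 136 per arm, d = .35 and correlation .5, power rises from .62 to .72. But the correction is stated for the ANOVAs, not the contrasts, and d = 2 × .175 is a two-group conversion, whereas f = .175 reproduces 681 only for three groups. I do not rest the point on those figures.

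**All five effects being real is the favourable case.** The protocol itself reports d = .21 for violent offenders in one cited study, and Hypothesis 2 expects smaller effects in the violent-crime pairing. This stands. With all five contrasts at d = .21 and correlation .5, power goes only from .20 to .24.

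**Conclusion.** The point holds as a cheap improvement. On the omnibus ANOVAs that the plan corrects, Holm adds about 8 to 10 points of power per outcome if all five effects are f = .175, and 3 to 4 points if three are. It adds essentially nothing if only one is real. The chance that all five are significant rises from .34-.45 to .62-.69. These figures rest on about 136 per arm, equal allocation, no exclusions and assumed correlations of .3 to .6.

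Two further readings go too far. A reader might infer that Holm brings power back to .95; it reaches at most about .85 per outcome at 136 per arm, and only when all five effects are real. A reader might also infer that Hypothesis 2 is affected; its equivalence bounds come from the observed effect sizes, not from which ANOVAs pass the correction.

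**What to change.** Under Confirmatory analyses, name Holm's step-down procedure at family-wise .05 in place of the Bonferroni correction, applied to the same five ANOVA p-values within each descriptor pairing. Under Sample size, keep α = .01: it is Holm's first step and so a conservative basis for planning.

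The cost is one sentence, with no extra participants and no new assumption. If intervals are reported at the Bonferroni level of 99%, add that they will not exactly mirror the step-down decisions. The change must be made before data are seen. The Sampling plan section says none had been collected at submission, and the Timeline section allows a week for requested changes. The mismatch between 681 and the five arms needs its own correction, which this change does not replace.

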### Timeline

We have already received ethics approval for the study (see attachment). The study is also already programmed in Qualtrics. We intend to commence data collection immediately after the Stage-1 registered protocol is accepted, allowing one week to implement requested changes, and expect to have received all data within two weeks. Data processing and analysis will be completed within three weeks, and we intend to complete the full report within three months of having received approval of the Stage-1 proposal.
